At the macro-level (health system level), the study assesses the costs and cost-effectiveness of the NCM from the perspectives of healthcare payers and participating primary care practices. It is hypothesized that the intervention may reduce healthcare expenditures through fewer ASE and more efficient utilization of healthcare services, while changes in practice organization and reimbursement structures may also generate economic benefits for participating practices.

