### The PRIMA intervention

The PRIMA intervention encompasses different elements at the practice level focusing on the aspects of continuity, comprehensiveness and subsidiarity of care provided by the practices (Fig 2). Core of the intervention is the introduction of PNs with their profession-specific competencies to the existing practice team. Intervention development was guided by the CCM. The PN introduces a NCM offering services beyond regular care currently provided. Within this NCM, the PN is to deliver seven defined tasks in the care for patients with chronic conditions, namely: 1. integration of PN into regular physician-led consultations, 2. conduct of initial and follow-up assessments to support comprehensive evaluation of care in the home setting, 3. coordination of care, 4. participation in interprofessional case conferences, 5. proactive monitoring of the care trajectory, 6. provision of patient education and 7. management of patient inquiries, including acute intervention in crisis. The intervention will be delivered over the full observation period, with a minimum duration of 12 months of follow-up per patient. In order to prepare the intervention, the PNs were employed six months in advance to the start of the intervention in January 2026. Three workshops of each two full days were held before the start of the intervention to prepare the PNs for the NCM. The workshops encompassed information on the PRIMA study and its design, including information and training for the seven tasks to be delivered. Furthermore, the workshop included topics like working in multiprofessional teams, communication skills and the own understanding of the PN role within the practice team. Prior to the start of the intervention, GPs and other team members were invited to participate in two so called “network meetings” providing the participating practice teams as a whole with relevant information regarding the conduct of the study. During the intervention phase, quality circles for the PNs take place on a monthly basis to support intervention delivery. Furthermore, during the first six months of the intervention, another two-day workshop will be held. As the role of the PN with defined tasks beyond regular care is novel to the practice teams, change management support is offered. All PN patient contacts are documented by the PN in a work diary during the intervention phase. Documentation includes baseline data (e.g., age, sex, date of inclusion, presence of inclusion criteria) and reason for contact, type of contact, activities performed, provided healthcare services, time expenditure (minutes), and, where applicable, additional comments in a free-text field. All elements of the intervention are delivered by the project partner IGES in collaboration with KVBW.

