### Outcomes

The primary outcome of PRIMA is the number of ASE after 12 months, identified using routine data from SHI physicians via standardized reimbursement codes (GOP). ASEs are defined as acute emergency contacts that are considered potentially avoidable through effective outpatient care and adequate disease management [22].

Secondary outcomes include measures of healthcare utilization, continuity and coordination of care, preventive service delivery, mortality data and economic outcomes. These are derived from routine data provided by KVBW and AOK BW.

Outcomes of the health economic evaluation include the costs of ambulatory care, defined as cumulative ambulatory care costs derived from claims data over a 12-month follow-up period, as well as intervention costs incurred during this period (including costs related to the PN intervention). In addition, cost-effectiveness will be assessed by relating total costs to the number of ASE.

Outcomes are assessed either over 12 months or across the full intervention period and obtained from routinely collected claims data made available by the KVBW and AOK BW following completion of the observation period. They are listed in Table 2 together with their respective data sources and assessment timeframes.

**Table 2 pone.0357117.t002:** Overview of study outcomes, data sources, and measurement periods.

Primary outcome				
Level	Outcome	Definition	Data source	Timeframe
Micro	Ambulatory care–sensitive emergencies (ASEs)	Number of ASEs identified via billing codes (GOP 01210 and 01212); indicator of potentially avoidable emergency care	KVBW routine data	12 months

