**Secondary outcomes – KVBW data**				
Micro	ASE per person-year	ASE rate adjusted for patient-specific observation time	KVBW	Intervention period
Micro	Patients with ≥1 ASE	Proportion of patients with at least one ASE	KVBW	12 months
Micro	Ambulatory emergencies	All emergency contacts independent of diagnosis	KVBW	12 months
Micro	Ambulatory emergencies per person-year	Rate-adjusted emergency contacts	KVBW	Intervention period
Micro	GP utilization	Number of GP contacts / quarters with GP visits	KVBW	Intervention period
Micro	Specialist utilization	Number of specialist contacts / quarters	KVBW	Intervention period
Meso	Treatment intensity	EBM points per patient and per practice	KVBW	Intervention period
Meso	Continuity of care	Continuity-of-Care Index (e.g., Bice–Boxerman)	KVBW	Intervention period
Meso	Care coordination	Number of providers; referral-based specialist visits	KVBW	Intervention period
Micro	Preventive care	Vaccination rates (influenza, pneumococcal, COVID-19)	KVBW	Intervention period
Macro	Outpatient costs	Cumulative outpatient costs incl. intervention costs	KVBW	12 months
Macro	Outpatient cost-effectiveness	Cost per outcome achieved	KVBW	12 months

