**Secondary outcomes – AOK Baden-Württemberg data**				
Macro	ASE + ambulatory-sensitive hospitalizations	Combined outpatient and inpatient avoidable emergency events	AOK BW	12 months
Macro	ASE + hospitalizations per person-year	Rate-adjusted combined events	AOK BW	Intervention period
Macro	Total emergencies	Diagnosis-independent emergency contacts	AOK BW	12 months
Macro	Total emergencies per person-year	Rate-adjusted total emergencies	AOK BW	Intervention period
Macro	Ambulatory-sensitive hospitalizations (ASH)	Potentially avoidable hospital admissions	AOK BW	12 months
Macro	ASH per person-year	Rate of ASH	AOK BW	Intervention period
Macro	Overall survival	Mortality data	AOK BW	Intervention period
Macro	Guideline adherence	Medication prescribing patterns	AOK BW	Intervention period
Macro	Total healthcare costs	All-cause expenditure	AOK BW	12 months
Macro	Overall cost-effectiveness	System-level cost-effectiveness	AOK BW	12 months

The PE encompasses outcomes on the micro- and the meso-level, namely participating patients and their relatives as well as the practice teams. The (PE) evaluation comprises both quantitative and qualitative measures. Table 3 gives an overview of the outcomes. All validated questionnaires have been used in primary care settings, targeting either interprofessional teams or patients with chronic conditions, aligning with the objectives of this study. Self-developed questionnaires were piloted with representatives of the target population using the think-aloud method to assess comprehensibility, relevance, and usability. Findings from the pilot testing informed revisions of the questionnaires before their use in the study [26].

**Table 3 pone.0357117.t003:** Outcomes of process evaluation on Meso and Micro Level.

Meso Level (Practice Teams)						
Outcomes	Instrument	B	T0	T1	T2	P
Job satisfaction	Warr-Cook-Wall (WCW) [40–42]	x		–	X	PT
Interprofessional Collaboration	Assessment of Interprofessional Team Collaboration Scale (AITCS-II) [7,43,44]	x		–	X	PT
Interprofessional Socialization	Interprofessional Socialization and Valuing Scale (ISVS 9a + 9b) [45,46]	x		–	x	PT
Implementation fidelity	Self-developed Questionnaire	–	–	–	x	PT
	PN documentation (activity logs)				x	PN
	Qualitative Case Study (interviews, focus groups, qualitative activity logs)			x	x	PT/C
PN training	Self-developed questionnaire based on ICAP model and Kirkpatrick levels [47–49]		x		x	PN

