### Health economic evaluation

The health economic evaluation will first assess the costs of ambulatory care within the IG from an ambulatory care payer perspective and relate these costs to the number of ASE. Results will be presented as incremental cost-effectiveness ratios (ICERs). Costs considered will include both project-specific costs (e.g., employment of the PNs and the PRIMA reimbursement model) and ambulatory healthcare expenditures reimbursed by SHI funds. Resource utilization will be derived from routine data and valued using standardized unit costs. Sensitivity analyses will be conducted to assess the robustness of the results, while statistical uncertainty of the ICERs will be estimated using cost-effectiveness acceptability curves. In addition to the SHI physician perspective, a separate analysis will be conducted from the perspective of participating general practices. This analysis will compare implementation-related costs (e.g., employment of PNs) with additional revenues generated through newly established reimbursement codes in order to assess the economic feasibility of the NCM.

For the population insured by AOK BW, total healthcare costs from the sickness fund perspective will be analyzed. In addition to ambulatory care costs, this analysis will include further sectors of care, such as inpatient care, medical aids and appliances, pharmaceuticals, rehabilitation services, and sickness benefits, where available in the routine data. These costs will subsequently be related to the number of ASE using ICERs. Additional sensitivity analyses and cost-effectiveness acceptability curves will be used to assess uncertainty in the economic evaluation.

All statistical analyses will be conducted in R (latest version; R Foundation for Statistical Computing) using RStudio or comparable tools, according to predefined standard operating procedures (SOPs).

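### The 12-month limit on intervention costs leaves the six-month nurse run-in out of the payer ICER, and the Health economic evaluation section does not state the same limit

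*Protocol article*

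**What the plan says.** **Time limit.** The first component of the economic outcome in the Outcomes section is "cumulative ambulatory care costs derived from claims data over a 12-month follow-up period". Intervention costs are the second component, and the text ties them to the same window: "as well as intervention costs incurred during this period (including costs related to the PN intervention". Table 2 repeats the window. The outpatient cost row, defined as "Cumulative outpatient costs incl. intervention costs", runs over 12 months, and so does the row for outpatient cost-effectiveness. In the AOK BW part of the table, total healthcare costs ("All-cause expenditure") and overall cost-effectiveness also have 12 months. The total-cost row does not name intervention costs.

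**Start-up.** The section on the PRIMA intervention says that "the PNs were employed six months in advance to the start of the intervention in January 2026", and that "Three workshops of each two full days were held before the start of the intervention". Two network meetings for the practice teams also came before the start. A further two-day workshop and monthly quality circles follow during the intervention phase.

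**No time limit.** The Health economic evaluation section builds the payer ICER from ambulatory expenditure plus costs specific to the project, with nurse employment and the PRIMA remuneration as examples. It gives no period for them. The separate practice analysis is to "compare implementation-related costs (e.g., employment of PNs) with additional revenues generated through newly established reimbursement codes", again with no period stated.

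**Aim.** According to the Introduction, "the study assesses the costs and cost-effectiveness of the NCM from the perspectives of healthcare payers and participating primary care practices".

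**The concern.** The early employment and the workshops were there to prepare the intervention. If the ICER counts only what is spent within a patient's 12 months, this preparation disappears from the cost side. Usual-care controls have no such run-in, so the omission acts in one direction: it lowers incremental cost and makes the model look cheaper per emergency averted.

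This matters because the article intends the findings to inform reimbursement of multiprofessional care. It names possible distortions of the economic evaluation in its limitations, but not this one. The sections also leave an analyst with two cost rules for the same ratio, one limited in time and one not. The choice between them could then be made after the data are seen.

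**Working it through.** The article states no cost, ICER or break-even figure, so there is nothing to reproduce. The check compares calendar windows and then works in nurse-months.

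**Step 1: overlap of the windows**
- Run-in: six months before January 2026, about July to December 2025 (The PRIMA intervention).
- Earliest patient window: from 1 January 2026 (Recruitment).
- Overlap: 0 months. The 3 × 2 = 6 workshop days before the start also fall outside.
- The later two-day workshop and the quality circles fall within the intervention phase and are not affected.

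**Step 2: size in nurse employment cost**

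Assumption: constant monthly cost per nurse. Relative addition = 6 / (months over which the run-in is spread). The 21 months are January 2026 to September 2027 (Study timeline); the longer periods are assumed.

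| Run-in spread over | Addition to nurse employment cost |
|---|---|
| one 12-month window, charged in full | 6/12 = 50% |
| 21-month intervention phase | 6/21 = 29% |
| 3 years | 6/36 = 17% |
| 5 years | 6/60 = 10% |
| 10 years | 6/120 = 5% |

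In the full-charge case the 12-month rule leaves out 6/(6 + 12) = 33% of nurse-months.

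**Step 3: illustration per emergency averted**

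Inputs from the Sample size calculation: about 112 patients per practice, 0.20 ASE per patient-year, 15% reduction. Further assumptions: one nurse per practice, and nurse employment as the only intervention cost.
- ASE averted per practice-year: 112 × 0.20 × 0.15 = 3.36.
- Nurse-months per ASE averted, 12-month rule: 12/3.36 = 3.57.
- Nurse-months per ASE averted, run-in charged in full: 18/3.36 = 5.36.

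**Step 4: why the net ICER can move by more**

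If savings elsewhere offset a share s of the 12-month nurse cost, full inclusion multiplies the net ICER by (1.5 − s)/(1 − s). For assumed s = 0, 0.25 and 0.50 this gives 1.50, 1.67 and 2.00. The article gives neither s nor any wage, so these are illustrations and not estimates.

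**Step 5: practice perspective**

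No window is stated and the analysis is not a row in Table 2. No figure follows for it.

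**The case against.** The strongest reply is that the Health economic evaluation section is the dedicated place for costing and sets no time limit. Its cost list could cover the run-in, and a journal article may leave write-off rules to the full analysis plan. The last part stands: the lack of an amortisation rule alone would be no finding. But the Outcomes section goes further than silence. It states a limit, and that limit excludes the run-in. Open wording elsewhere does not remove it; it shows that the two sections differ.

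A reader might infer that the run-in falls outside every cost window in the plan, and that the practice feasibility result is therefore too favourable as well. The document does not support this. The practice analysis is described as separate, is not tied to the 12-month follow-up, and refers to costs of implementation, which may well include start-up employment. Its window is unspecified, and no exclusion has been shown.

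Three further objections stand:
- Part of the pre-start activity informed staff about the study and its conduct. That part is arguably a research cost and not a cost of the model.
- The document does not say who paid the nurses before January 2026, or that a later adopter would need six months.
- The 50% figure is the extreme case. Spread over the assumed longer periods, the addition is much smaller, and nothing in the document makes 21 months the natural base case.

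**Conclusion.** The point holds for the payer cost and ICER outcomes. As the Outcomes section and Table 2 are worded, six months of nurse employment and three workshops are left out of the numerator. The omission favours the new model, and the Health economic evaluation section does not state the same limit. For the practice analysis, the most that can be said is that its window is not stated.

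The omitted amount is six nurse-months per nurse: 50% of nurse employment cost in the upper case, 29% over the intervention phase, and 17% to 5% over an assumed 3 to 10 years. This rests on a constant monthly nurse cost, and the workshops are not priced. The direction is clear. The effect on the ICER in euros is not derivable, because the document gives no wages and no share of nurse cost in incremental cost.

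**What to change.** Reconcile the Outcomes section, Table 2 and the Health economic evaluation section before the analysis phase begins in October 2027:

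1. Add a distinct start-up cost item for nurse employment and model-related training before January 2026. Separate it from the cost of informing staff about the study.
2. Report the payer ICER with and without this item, over a stated range of write-off periods that includes 21 months and longer ones. State whose budget carries each part.
3. State the window of the practice cost-versus-revenue comparison, and that it includes the start-up costs that the practice bears.

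The cost is a change of wording and a little more analysis. Nurse employment has to be costed in any case, but the pre-start salary and training amounts must be obtained. The downside is a less favourable ICER and possibly a less favourable practice break-even.

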**Secondary outcomes – KVBW data**				
Micro	ASE per person-year	ASE rate adjusted for patient-specific observation time	KVBW	Intervention period
Micro	Patients with ≥1 ASE	Proportion of patients with at least one ASE	KVBW	12 months
Micro	Ambulatory emergencies	All emergency contacts independent of diagnosis	KVBW	12 months
Micro	Ambulatory emergencies per person-year	Rate-adjusted emergency contacts	KVBW	Intervention period
Micro	GP utilization	Number of GP contacts / quarters with GP visits	KVBW	Intervention period
Micro	Specialist utilization	Number of specialist contacts / quarters	KVBW	Intervention period
Meso	Treatment intensity	EBM points per patient and per practice	KVBW	Intervention period
Meso	Continuity of care	Continuity-of-Care Index (e.g., Bice–Boxerman)	KVBW	Intervention period
Meso	Care coordination	Number of providers; referral-based specialist visits	KVBW	Intervention period
Micro	Preventive care	Vaccination rates (influenza, pneumococcal, COVID-19)	KVBW	Intervention period
Macro	Outpatient costs	Cumulative outpatient costs incl. intervention costs	KVBW	12 months
Macro	Outpatient cost-effectiveness	Cost per outcome achieved	KVBW	12 months
**Secondary outcomes – AOK Baden-Württemberg data**				
Macro	ASE + ambulatory-sensitive hospitalizations	Combined outpatient and inpatient avoidable emergency events	AOK BW	12 months
Macro	ASE + hospitalizations per person-year	Rate-adjusted combined events	AOK BW	Intervention period
Macro	Total emergencies	Diagnosis-independent emergency contacts	AOK BW	12 months
Macro	Total emergencies per person-year	Rate-adjusted total emergencies	AOK BW	Intervention period
Macro	Ambulatory-sensitive hospitalizations (ASH)	Potentially avoidable hospital admissions	AOK BW	12 months
Macro	ASH per person-year	Rate of ASH	AOK BW	Intervention period
Macro	Overall survival	Mortality data	AOK BW	Intervention period
Macro	Guideline adherence	Medication prescribing patterns	AOK BW	Intervention period
Macro	Total healthcare costs	All-cause expenditure	AOK BW	12 months
Macro	Overall cost-effectiveness	System-level cost-effectiveness	AOK BW	12 months

The PE encompasses outcomes on the micro- and the meso-level, namely participating patients and their relatives as well as the practice teams. The (PE) evaluation comprises both quantitative and qualitative measures. Table 3 gives an overview of the outcomes. All validated questionnaires have been used in primary care settings, targeting either interprofessional teams or patients with chronic conditions, aligning with the objectives of this study. Self-developed questionnaires were piloted with representatives of the target population using the think-aloud method to assess comprehensibility, relevance, and usability. Findings from the pilot testing informed revisions of the questionnaires before their use in the study [26].

**Table 3 pone.0357117.t003:** Outcomes of process evaluation on Meso and Micro Level.

Meso Level (Practice Teams)						
Outcomes	Instrument	B	T0	T1	T2	P
Job satisfaction	Warr-Cook-Wall (WCW) [40–42]	x		–	X	PT
Interprofessional Collaboration	Assessment of Interprofessional Team Collaboration Scale (AITCS-II) [7,43,44]	x		–	X	PT
Interprofessional Socialization	Interprofessional Socialization and Valuing Scale (ISVS 9a + 9b) [45,46]	x		–	x	PT
Implementation fidelity	Self-developed Questionnaire	–	–	–	x	PT
	PN documentation (activity logs)				x	PN
	Qualitative Case Study (interviews, focus groups, qualitative activity logs)			x	x	PT/C
PN training	Self-developed questionnaire based on ICAP model and Kirkpatrick levels [47–49]		x		x	PN
Implementation Outcomes Barriers & Facilitators Role Transformation	Qualitative Case Study (interviews, focus groups, qualitative activity logs)		x	x	x	PT/C
Practice Characteristics	Self-developed questionnaire	x				
**Micro Level (patients and their relatives)**						
Quality of life	EQ-5D-5L [50–53]	–	X	–	x	P
Self-Efficacy	Self-Efficacy-Scale (SES6G) [54]	–	X	–	x	P
Subjective symptoms and treatment satisfaction	Measure Yourself Medical Outcome Profile (MYMOP) [55,56]	–	X	–	x	P
Satisfaction with care by PN	Nurse Practitioner Satisfaction Survey (NPSS) [57,58]	–	–	–	x	P
Patients assessment of chronic illness care	PACIC short [59–63]	–	x		x	P
Patients’ experiences of the new model of care	Qualitative Case Study	–	–	–	x	P/R

B: Baseline, Start of NP in Practice Teams, T0: Start of Intervention, T1: Mid Intervention, T2: End of Intervention; ICAP: Interactive –Constructive-Active-Passive; P: Population, PT: Practice Team; PN: Prima nurse, C: collaborators; R: relatives

### Data

Regarding the effectiveness analysis and economic evaluation, routinely collected healthcare data will be used. Data sources include routine data from KVBW and AOK BW for the reporting period from 01 January 2024–30 September 2027. KVBW includes patient core data, information on participation in the GP-centered care model collected via the study consent form, practice core data, regional indicators, and outpatient claims data. For the subset of AOK BW-insured patients, patient master data, data on outpatient and inpatient care, pharmaceutical prescriptions, remedies and medical aids, long-term care, rehabilitation, sick leave, transportation costs, and domestic help are provided by AOK BW.

Written informed consent will be obtained from all patients participating in the IG prior to inclusion in the study and prior to the transfer and use of routinely collected healthcare data for research purposes. Only routinely collected healthcare data necessary for the predefined analyses will be requested and processed in accordance with the principle of data minimization. KVBW data will be provided as separate datasets for intervention and control groups. A matched CG will be generated from KVBW data based on criteria defined by the evaluator. AOK BW data will be provided as a pre-matched dataset, with matching performed by AOK BW prior to data delivery. Datasets from KVBW and AOK BW will not be linked or merged, as all outcomes are pre-specified to be analyzed within their respective datasets.

Data extraction follows routinely implemented administrative processes and is performed on a quarterly and continuous basis. Data completeness, validity and quality are ensured by standard validation procedures at the respective data providers, and additional plausibility and validity checks are performed at the Technical University of Munich (TUM) data trust office prior to analysis.

Data from both providers are pseudonymized prior to transfer. A double-pseudonymization procedure is applied by the TUM data trust office, replacing study pseudonyms with evaluation pseudonyms to prevent re-identification. The corresponding linkage key is stored under trustee responsibility and is not accessible to the evaluators. Data transfer to the evaluator is performed via secure, encrypted channels and external encrypted storage media, with access restricted to authorized personnel. Fig 3 illustrates the data flow.

